## Abstract

Around 14% of pregnancies globally are affected by gestational diabetes mellitus (GDM), making it one of the most common disorders experienced by women in pregnancy. While dietary, physical activity and supplement interventions have been implemented to prevent GDM, with varying levels of success, altering the gut microbiota through diet is a promising strategy for prevention. Several studies have demonstrated that women with GDM likely have a different gut microbiota to pregnant women without GDM, demonstrating that the gut microbiota may play a part in glycemic control and the development of GDM. To date, there have been no randomized controlled trials using diet to alter the gut microbiota in pregnancy with the aim of preventing GDM. Here, we present the study protocol for a single-blind randomized controlled trial which aims to determine the effectiveness of the *Healthy Gut Diet* on reducing the diagnosis of GDM in pregnant women with one or more risk factors. Consenting women will be randomized into either the *Healthy Gut Diet* intervention group or the usual care (control) group after 11 weeks gestation. The women in the intervention group will receive three telehealth counseling appointments with an Accredited Practicing Dietitian with the aim of educating and empowering these women to build a healthy gut microbiota through their diet. The intervention was co-designed with women who have lived experience of GDM and incorporates published behavior change techniques. The control group will receive the usual care and will also be shown a brief (3 min) video on general healthy eating in pregnancy. The primary outcome is the diagnosis of GDM at any stage of the pregnancy. Secondary outcomes include changes to gut microbiota composition and diversity; gestational weight gain; maternal and infant outcomes; management of GDM (where relevant); dietary quality and intake; physical activity; and depression scoring. We aim to recruit 120 women over 16 months. Recruitment commenced in January 2023. The trial has been registered with the Australian New Zealand Clinical Trials Registry (ACTRN12622001285741).

## 1. Introduction

Gestational diabetes mellitus (GDM) is a common and costly condition that occurs during pregnancy. Globally, the prevalence of GDM is estimated to be around 14% [1]. In Australia, GDM incidence has doubled in the decade since 2010 and affects one in six Australian pregnancies [2,3]. Although much of this increase has been due to changes to the diagnostic criteria, certain risk factors increase the risk of developing GDM [4]. Up to 70% of women with GDM will develop it again in subsequent pregnancies [5]. The effects of GDM are intergenerational. Women with GDM have a 10-fold increased risk of type 2 diabetes [6] and a 2-fold risk of cardiovascular events [7]. Their children are more likely to develop cardiometabolic conditions and to experience obesity [8].

Medical nutrition therapy and physical activity, together with self-monitoring of blood glucose levels, are the cornerstone of GDM management; however, around 50% of women will require pharmacological intervention in the form of oral hypoglycemic agents or insulin [9]. Strong predictors of GDM include early excess gestational weight gain (GWG), a pre-pregnancy body mass index (BMI) above 25 kg/m^2^, and a history of GDM [5,10,11]. Several studies have demonstrated a positive effect of dietary intervention for the prevention of GDM [12] but have not consistently shown reductions in GDM risk [13].

The gut microbiota—the community of microorganisms in the human digestive system—play a role in glycemic control in GDM [14]. Although not consistently demonstrated in all studies, recent evidence shows that women with GDM may have significantly different microbiota compositions to women without GDM [15] with similarities to the non-pregnant population with type 2 diabetes [14,16,17,18,19]. The gut microbiota can be modified by a range of factors, including diet, dietary supplements, physical activity, pregnancy hormones, and antibiotics [20,21]. Although diet can rapidly alter the gut microbiota, particularly in the short term [21], few studies have investigated the link between diet, the maternal gut microbiota and the development of GDM. One observational study has shown that adherence to a standard GDM diet produced better metabolic and inflammatory outcomes, which are associated with significant differences in gut microbiota composition [22]. While it seems promising that dietary interventions designed to modulate the gut microbiota may produce favorable pregnancy outcomes, there is a clear lack of evidence on the impact of dietary interventions designed to improve gut microbiota composition and the development of GDM.

A healthy gut diet is abundant in fiber-rich, prebiotic whole foods found exclusively in vegetables, fruit, whole grains, legumes/lentils, nuts, and seeds [23]. A healthy maternal diet plays an influential role in epigenetic programming, affecting the health of the next generation [24]. Recent evidence shows that pregnant women counseled to ‘eat for their gut’ have improved diet quality [25]. Dietary interventions that target the maternal gut microbiota show potential to reduce the health burden associated with GDM. Although modulating the gut microbiota shows promise for the prevention of GDM [12], specific interactions between dietary components and changes to gut microbiota function in early pregnancy remain unexplored.

The primary aim of this study is to determine the effectiveness of a dietary intervention called ‘*The Healthy Gut Diet*’ on reducing the diagnosis of GDM in pregnant women with one or more specified risk factors. We hypothesize that there will be fewer women diagnosed with GDM in the intervention group and this effect will be enhanced amongst women who adhere closest to the dietary recommendations. The secondary aim is to understand whether dietary intervention can modulate the gut microbiota compared with the usual care group and if this effect is enhanced in women who closely adhere to the dietary intervention compared to those who are less adherent. The third aim is to compare the maternal and infant outcomes of women enrolled in the dietary intervention and those in the usual care group.

## 2. Materials and Methods

### 2.1. Design

This study is a pilot single-blind, two-arm, parallel randomized controlled trial conducted to test the effect of the dietary intervention for pregnant women at risk of developing GDM. We will aim to recruit 120 women in total, who will be randomly allocated into the intervention or control group. The study flow diagram is shown in Figure 1.

### 2.2. Setting

The study is open to all pregnant women who meet the criteria who are birthing at public or private maternity facilities in Queensland, Australia. Geographically, Queensland is the second-largest state/territory and third-most populous state in Australia. Between 60,000 and 62,000 babies are born in Queensland annually. Nationally, the incidence of GDM is 16% [2].

### 2.3. Eligibility Criteria

Pregnant women, 18 years or older, with a singleton pregnancy are eligible if they enroll in the study prior to 18 weeks gestation, and have one or more of the following risk factors for developing GDM: prior history of GDM; a first-degree relative with type 2 diabetes mellitus or a mother/sister with a history of GDM; pre-pregnancy body mass index (BMI) greater than 25 kg/m^2^; or a biological child who weighed more than 4000 g at birth.

### 2.4. Exclusion Criteria

Women will be excluded if they have a confirmed diagnosis of any form of diabetes (including GDM) at the time of enrolment. Due to the complex or confounding nature of certain conditions, women with reported cystic fibrosis, inflammatory bowel disease, bariatric surgery or bowel disorder requiring a restrictive diet, a diagnosed eating disorder, or other complex medical co-morbidities (for example, kidney or heart disease) will also be excluded. Assisted conception (for example in vitro fertilization) is not an exclusion criterion. Women who are unable to understand the intervention (e.g., have insufficient understanding of spoken English) are also excluded.

### 2.5. Recruitment

As this is a state-wide study, multiple recruitment strategies have been used. The primary strategies are ongoing, paid social media advertisements from the study’s Instagram and Facebook pages, targeting women between 18 and 50 years in Queensland. Antenatal care providers (obstetricians, general practitioners, and midwives) have also been targeted via study information, flyers and business-card sized ‘referral cards’ sent to public and private clinical and special interest networks and cold-contacting private practices via email and postal mail. This second strategy recognizes that one of the more successful recruitment strategies for trials is referrals from trusted health care professionals [26]. Women can also be identified upon referral to the study hospitals (two small metropolitan hospitals). Other recruitment strategies involve putting flyers in doctor’s surgeries, maternal and child health centers, childcare, playgroups, shopping centers, and toy libraries. Women who have consented to be contacted, either verbally at participating study sites or by completing the online ‘Register Your Interest’ form, are sent an SMS inviting them to participate in the study.

### 2.6. Randomisation and Blinding

Randomization of a 1:1 group allocation ratio with randomly permuted blocks was generated prior to the study recruitment commencing and stored in electronic sealed envelopes. Following an eligibility check, the study lead allocates each new enrolled participant by selecting the next ‘sealed envelope’. Participant blinding is not possible due to the nature of a dietary intervention. The researchers involved in data analysis will be blinded to the group allocation. Only the study lead, who will not be directly involved in data analysis, will be aware of the participant group allocation until analysis is completed.

### 2.7. Participation

Women in both groups receive an AUD 50 grocery store gift voucher after completing the baseline questionnaire and trimester 2 dietary intake records, and a second AUD 50 grocery store gift voucher will be received upon completion of the 36-week questionnaire and trimester 3 dietary intake records. All participants will be invited to complete a 12-week post-partum follow-up questionnaire and will receive a third AUD 25 grocery store gift voucher upon completion. Women in the intervention group will also be invited to participate in a short phone interview that will explore the barriers and enablers of the Healthy Gut Diet (both within pregnancy and longer term). Women who undertake gut microbiota analysis will receive a personalized report (Insight report) generated by a third-party laboratory, Microba [27].

### 2.8. Changes to Protocol (Eligibility and Recruitment)

This study was initially targeted at pregnant women with a history of GDM (but free from diagnosis at enrolment) who were birthing at either one of two small metropolitan, public birthing facilities (study sites). However, after 3 months of recruitment, only one woman had enrolled to participate (the target was 12 at that timepoint). The study team then made changes to both the eligibility criteria and the recruitment method to improve recruitment rates (as outlined earlier). At the time of submitting this publication, recruitment has been open for eight months and 62 women have enrolled.

### 2.9. Intervention

The intervention is a multi-component dietary intervention that has been co-designed with mothers who have lived experience of GDM. It is expected that the co-design process will increase the intervention’s feasibility and acceptability and assist with the behavior change technique selection through a ‘behavior diagnosis’. The results of this process will be reported elsewhere. The objective of the intervention is to educate, motivate, and empower pregnant mothers and equip them with the skills and self-efficacy to make dietary changes that target the gut microbiota. The target behavior is *eating for gut health.* The women enrolled in the study receive one initial counseling session via telehealth and two follow- up support sessions (phone call or telehealth), as well as weekly text messages, supporting educational material and resources, and access to a private Instagram page and a private Facebook support group. To better describe each of the intervention components and in line with the Medical Research Council’s recommendation, the TIDieR Checklist [28] has been used and is available as Supplementary Material.

#### 2.9.1. Dietary Recommendations

The target behavior, ‘*eating for gut health*’ is described based on three main healthy gut diet principles:Include a variety of plant foods (minimally processed) at each meal;Reduce the intake of ultra-processed foods and foods high in saturated fat;Eat naturally fermented foods.

Counseling is undertaken by an Accredited Practicing Dietitian, who is specifically trained to deliver the dietary intervention, in line with the Australian Dietary Guideline recommendations for pregnant women [29].

It is anticipated that women who consume a greater diversity of plant-based and fermented foods per week will have more diverse gut microbiota profiles compared with women who have low diversity and consume no fermented foods [23,30]. High intake of fiber and lower intake of ultra-processed foods and foods that are high in saturated fat is expected to result in lower levels of Gram-negative bacteria, such as the genus-level bacteria *Parabacteroides, Prevotella*, *Haemophilus* and *Desulfovibrio* [17], and higher levels of Short-Chain Fatty Acid-producing bacteria, including the species *R. Bromii* and *A. Putredinis* [31,32].

#### 2.9.2. Intervention Procedures

Following consent and enrolment, women are sent a link to book a telehealth appointment with the intervention dietitian. Ideally, the first appointment (approximately 45 to 60 min in length) is attended within 1 to 2 weeks of enrolment and must occur before 18 weeks gestation (but not before 12 weeks gestation). Intervention content and procedures are outlined in Supplementary Table S1: Item 2. Women are encouraged to set three dietary behavior goals at the initial appointment, in alignment with the three Healthy Gut Diet recommendations. At each follow-up, progress towards the goals is reviewed with the dietitian and revised where necessary. For intervention fidelity, each appointment will follow a pre-defined script with a fidelity checklist to ensure all participants receive the same information. The study lead, also an Accredited Practicing Dietitian, randomly selects two counseling sessions per month to attend as an observer to further assess fidelity of intervention delivery.

#### 2.9.3. Behavior Change Techniques

A range of behavior change techniques (BCTs) have been integrated into the intervention, largely informed by the intervention co-design process. These have been mapped to a published taxonomy [33] and are shown in Table 1.

### 2.10. Usual Care (Control Group)

Participants in both groups undertake all usual antenatal appointments according to their selected model of antenatal care. The control group also receives a 3 min video providing brief advice on general healthy eating in pregnancy according to the Australian Dietary Guideline [29] recommendations and a link to the electronic version of the Guidelines. Women in the control group complete all data collection tasks but do not see the study dietitian or receive additional support such as text messages or access to private social media pages.

### 2.11. Data Collection

Data are collected at various time points, as shown in Table 2. Following consent, enrolment and randomization, all women complete online questionnaires at the beginning of the study (within 1 week of enrolment) and at 36 weeks gestation. The women will also be invited to complete a follow-up questionnaire at 12 weeks postpartum. The questionnaires, delivered via REDCap, will collect information on:Demographic data;Dietary intake (using the Short Dietary Questionnaire);International Physical Activity Survey [34];Edinburgh Postnatal Depression Score [35];Previous GDM diagnosis and management (where relevant);Intake of dietary supplementation, probiotics and antibiotics;Self-reported height and pre-pregnancy weight.

A separate paid questionnaire, known as the Australian Eating Survey (AES) (hosted by the University of Newcastle), is sent from the survey dashboard upon enrolment and at 36 weeks gestation [36]. The AES is a semi-quantitative Food Frequency Questionnaire validated for use in Australian Adults [36]. It is a self-administered tool used to collect information on estimated dietary intake over the last 3–6 months through 120 dietary items assessing frequency of consumption, from never to ≥seven times per day [36]. It provides information on food, food groups, macro and micronutrient consumption, and alignment with the Australian Dietary guidelines [36].

Dietary behavior goals set by women in the intervention group will be recorded at the initial counseling appointment by the dietitian. Women will be contacted at two time points in trimester 2 and 3 to complete a 24 h recall with a trained dietitian, using the multi-pass method. Maternal and infant outcome data, including GDM diagnosis and gestational weight gain, will be collected from medical records. At baseline and 36 weeks, women will provide stool samples using a self-collection sample kit provided by Microba Life Sciences [27]. Microba is a precision microbiota science company that will be providing high quality taxonomic, functional data and sample quality metrics from the microbiota sampling kits. Microba use shotgun metagenomic sequencing using the NovaSeqTM 6000 (Illumina, San Diego, CA, USA) with 2 × 150 bp paired-end chemistry at a target depth of 3 Gb per sample. Species classification will be determined with the Microba Community Profiler (v2), which uses a curated set of genome sequences from the public domain and Microba proprietary data (Microba Genome database, MGDB) a validated pipeline for producing comprehensive and accurate species profiles of human gastrointestinal samples [27]. All data (excluding microbiota data) will be collected and stored using the online data capture tool called REDCap 13.10.6.

### 2.12. Ethical Considerations and Monitoring

The study was approved by the Metro North Committee A Human Research Ethics Committee (HREC/2021/QRBW/82350) and the University of Queensland Human Ethics Committee. Current protocol version 1.8. 17 March 2023. As this study a dietary intervention only with no medication or supplementation, minimal harm is expected. No data monitoring or trial auditing procedures were developed. Any adverse events will be reported to the approving Human Research Ethics Committee in accordance with reporting requirements of the HREC and The University of Queensland.

### 2.13. Statistical Methods

The study results will be reported as per the Consolidated Standards of Reporting Trials (CONSORT) guidelines [37]. Results will be reported using an intention-to-treat approach, so all women in the intervention arm will be included in the primary analysis. In a sensitivity analysis, a per protocol approach will be used. Data from women who did not complete at least two of the three dietary counseling sessions will be excluded from this analysis. For the primary outcome (Section 2.13.1), comparisons between the groups using the binary outcome of GDM or no GDM diagnosis will be conducted using chi-square analysis. Logistic regression models will be used to adjust for potential confounders, decided a priori using causal diagrams. Confounders will include age, parity, pre-pregnancy BMI (categorical), weight gain above the Institute of Medicine recommendations based on pre-pregnancy BMI [38], assisted conception, and antibiotic use.

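### The per-protocol sensitivity analysis can exclude women from the intervention arm only, so it compares self-selected attenders with all controls and is not a randomised comparison

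*Protocol article*

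**What the plan says.** Section 2.13 (Statistical Methods) sets the primary approach: "Results will be reported using an intention-to-treat approach, so all women in the intervention arm will be included in the primary analysis". It then adds a second analysis: "In a sensitivity analysis, a per protocol approach will be used". The set for that analysis is fixed in one sentence: "Data from women who did not complete at least two of the three dietary counseling sessions will be excluded from this analysis".

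The sessions belong to one arm. The Abstract states: "The women in the intervention group will receive three telehealth counseling appointments with an Accredited Practicing Dietitian". Section 2.10 (Usual Care) states: "Women in the control group complete all data collection tasks but do not see the study dietitian". The article gives no matching completion criterion for controls.

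Allocation is described in Section 2.6 as "Randomization of a 1:1 group allocation ratio with randomly permuted blocks". With the target of 120 women, that is about 60 per arm.

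**The concern.** Taken literally, the rule would delete the whole control arm, because every control has zero sessions. That cannot be meant and needs only a clarification of wording. The workable reading applies the rule to intervention women alone, and this is where the statistical problem lies. Intervention women who disengage are dropped, while control women who would have disengaged if offered sessions stay in and cannot be identified. The two groups compared are then no longer alike by design.

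Whether this biases the result depends on whether attendance is related to GDM risk. Two routes are possible. Attendance may follow motivation or baseline risk. Also, a GDM diagnosis at any stage counts as an outcome, and the article does not date the two follow-up sessions. A woman diagnosed before her second session who then stops attending would be removed as a case, and only from the intervention arm. The documents give no size for either route.

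The planned adjustment is not shown to repair this. The covariates in Section 2.13 are maternal age, BMI before pregnancy, parity, excess weight gain, antibiotics and assisted conception. Prior GDM and family history, both eligibility risk factors in Section 2.3, are not among them, nor is any direct measure of engagement.

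At stake is how a null primary result beside a more favourable per-protocol result would be read, in a pilot whose estimates are meant to inform later sample sizes.

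**Working it through.** The plan states no figure for this analysis, so there is none to reproduce. The check asks what the contrast would show if the diet had no effect.

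**Inputs**
- From the documents: 1:1 allocation of 120 women, so 60 per arm; GDM analysed as a binary outcome by chi-square.
- Assumed: overall GDM risk *p* = 0.30. The documents give 16% nationally and 50% for the original prior-GDM population, so both ends are also shown.
- Assumed: share *q* of intervention women excluded, 0.2 or 0.3.
- Assumed: ratio *r* of GDM risk in the excluded women to that in the retained women, 1.5 or 2.

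**Formula.** With no effect, both arms have overall risk *p*. In the intervention arm, *p* = (1 − *q*) × retained risk + *q* × *r* × retained risk. Hence

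retained risk = *p* / ((1 − *q*) + *q* × *r*).

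The controls stay at *p*.

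**Results at p = 0.30 (true difference 0)**

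| q | r | Retained risk | Per-protocol difference | Two-sided rejection |
|---|---|---|---|---|
| 0.2 | 1.5 | 0.30/1.10 = 0.273 | -2.7 points | 6.0% |
| 0.2 | 2 | 0.30/1.20 = 0.250 | -5.0 points | 8.7% |
| 0.3 | 1.5 | 0.30/1.15 = 0.261 | -3.9 points | 7.0% |
| 0.3 | 2 | 0.30/1.30 = 0.231 | -6.9 points | 11.6% |

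Rejection rates use the pooled two-proportion test at a nominal 5%, with 48 or 42 retained women against 60 controls.

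**Sensitivity to the assumptions**
- Other base rates, at *q* = 0.3 and *r* = 2: *p* = 0.16 gives -3.7 points (rejection 7.7%); *p* = 0.50 gives -11.5 points (rejection 20.8%).
- No association, *r* = 1: the bias is 0.
- Low attenders at lower risk, *r* = 0.67, *q* = 0.2, *p* = 0.30: 0.30/0.934 = 0.321, or about +2 points, against the diet.

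**Bias against random error.** With 48 against 60 women at 30% risk, the standard error is √(0.21 × (1/48 + 1/60)) = 0.089. A bias of 2.7 to 5.0 points is then about 0.3 to 0.6 standard errors.

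**The alternative.** Controls have no access to sessions, so the complier-average estimate is the intention-to-treat risk difference divided by (1 − *q*). With no effect it is 0/0.8 = 0 or 0/0.7 = 0. If the attendance share is treated as known, the estimate and its interval are scaled by 1/0.8 = 1.25 or 1/0.7 = 1.43.

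**The case against.** The best reply is that the plan already contains the problem: intention-to-treat is primary, per-protocol is labelled a sensitivity analysis, and the trial is a pilot. A non-randomised contrast is a known limitation of per-protocol analysis whenever controls receive no sessions. All of that stands and limits the weight of the point. It does not make the rule sound. The exclusion is written into the article rather than left to a further document, and a better analysis of the same data is available.

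A reader might infer that the analysis must favour the diet. The documents do not support that. They give no attendance data and nothing on the risk of low attenders. Women with prior GDM could well be the most motivated to attend, which would reverse the sign. The figures above are also crude, and adjustment for age, parity and BMI might remove part of any bias.

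A reader might also infer that this contrast is the planned test of the Introduction's hypothesis that "this effect will be enhanced amongst women who adhere closest to the dietary recommendations". No section says so. That hypothesis concerns adherence to the diet, not attendance. The adherence measures the article defines, in Section 2.13.4, are dietary scores applied to the microbiota. The per-protocol result could be misread as evidence on the hypothesis, but the plan does not assign it that role.

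The complier-average estimate has limits too. It assumes that allocation has no effect in women who attend too few sessions. Section 2.9 provides weekly texts, educational resources and private social media pages, which may reach those women.

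**Conclusion.** The point holds as a defect of a sensitivity analysis. The exclusion can act in one arm only, so the per-protocol contrast is not randomised. This follows from the article's own text and needs no assumption.

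The size does rest on assumptions. At 30% GDM risk, 20–30% excluded and low attenders at 1.5 to 2 times the risk of attenders, an inert diet would show -2.7 to -6.9 points, and the test would reject in 6.0% to 11.6% of trials instead of 5%. The bias disappears at a ratio of 1 and changes sign below 1. The primary intention-to-treat analysis is unaffected. The change is worth making, but it does not put the trial's main result in doubt.

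**What to change.** Keep intention-to-treat as the primary analysis and change the sensitivity analysis as follows.

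- Replace the exclusion with a complier-average causal effect estimate of the GDM risk difference in all randomised women. Use allocation as the instrument and attendance at two or more of the three sessions as receipt.
- Repeat it with attendance at any session as receipt.
- If the per-protocol comparison is kept beside it, state that the exclusion applies to the intervention arm only and label the result non-randomised.
- Count attendance over the whole schedule. Cutting it off at GDM diagnosis would make receipt depend on the outcome, because an early diagnosis limits how many sessions can count.
- State that neither estimate tests whether the effect is greater in close adherers. Intention-to-treat divided by the attending share is never smaller in magnitude than intention-to-treat, so an enhanced effect would appear by construction.

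The cost is a little analysis work; the session counts are needed for the existing rule anyway. There are two downsides to state. The confidence interval is wider, by a factor of about 1.25 to 1.43 if 70–80% attend. The estimate also assumes that allocation has no effect in low attenders, which is doubtful here. The any-session version checks that only partly, because texts, resources and social media access may also reach women who attend no session.

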### 2.14. Sample Size

The initial sample size calculation was based on the original eligibility criteria (previous GDM diagnosis), which assumed a background incidence of 50% (35 to 80% of women with a prior GDM diagnosis will develop it in subsequent pregnancies [46]). The original recruitment target of 40 women per group provided 80% power to detect a difference of 50% diagnosis rate in the control group and 25% in the intervention group (with a two-sided 5% significance level). However, as the changes to protocol outlined in Section 2.8 to include women with one or more risk factors for GDM have variably altered the background incidence of GDM, it is difficult to estimate the sample size needed for this trial. Therefore, a target of 120 women has been set on the basis that this is a pilot RCT, considering how many participants we can feasibly recruit within the study’s budget and timeline.

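### The a priori covariate list for the GDM model omits prior GDM, a strong predictor already collected; the cost is some precision, not bias

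*Protocol article*

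**What the plan says.** **Analysis (Section 2.13).** For the primary outcome, "comparisons between the groups using the binary outcome of GDM or no GDM diagnosis will be conducted using chi-square analysis". Logistic regression then adjusts for covariates said to be chosen a priori from causal diagrams: "Confounders will include age, parity, pre-pregnancy BMI (categorical), weight gain above the Institute of Medicine recommendations based on pre-pregnancy BMI", followed by assisted conception and antibiotic use. That makes six, and prior GDM is not one of them.

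**Prior GDM elsewhere in the same article.**
- Section 1 names it among three main predictors: "Strong predictors of GDM include early excess gestational weight gain (GWG), a pre-pregnancy body mass index (BMI) above 25 kg/m^2^, and a history of GDM".
- Section 2.14 gives its strength: "35 to 80% of women with a prior GDM diagnosis will develop it in subsequent pregnancies". The first sample-size calculation took 50%.
- Section 2.3 makes it one of several alternative routes into the trial: women must "have one or more of the following risk factors for developing GDM: prior history of GDM", a family history, a BMI above 25, or a previous child above 4000 g.
- Section 2.11 lists it among the questionnaire items: "Previous GDM diagnosis and management (where relevant").

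**Allocation (Section 2.6).** "Randomization of a 1:1 group allocation ratio with randomly permuted blocks was generated prior to the study recruitment commencing", with the next sealed envelope used for each new participant. No stratification factor is named.

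**The concern.** Section 2.8 explains that the trial first sought only women with a history of GDM. In that population prior GDM is the same for everyone and needs no adjustment. After the widening it separates women with roughly even odds of GDM from women at lower risk, and Section 4 accepts that background incidence now depends on the risk factors present. The covariate list does not reflect this change.

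As described, neither the allocation, the chi-square nor the logistic model takes account of prior GDM. Parity is a weak substitute, because it does not separate parous women with prior GDM from parous women without it. At stake are some precision, and an observed difference that may partly reflect which arm happened to receive more women with prior GDM. Section 4 says the trial may be underpowered and that its estimate will feed later sample-size calculations, so precision matters here.

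**Working it through.** The plan gives no figure on this point, so there is none to reproduce. (Separately, 50% versus 25% with 40 per group gives 64% power by the usual two-sided normal approximation, not the stated 80%. Nothing below depends on that.)

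**Inputs from the article.** Target 120 at 1:1, so 60 per arm (Sections 2.6 and 2.14). Recurrence 50%, range 35 to 80% (Section 2.14). Two-sided 5% level (Section 2.14). National GDM incidence 16% (Section 2.2).

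**Assumptions, not in the article.**
- Share with prior GDM: 40%, with 20 to 50% also shown for imbalance.
- Risk in women without prior GDM: 16 to 30%. The 16% covers all pregnancies, while these women each have another risk factor, so it is probably a low value.
- Treatment effect: the odds ratio of the original 25% versus 50%, (0.25/0.75)/(0.50/0.50) = 1/3, in both groups of women.

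**Step 1: size of chance imbalance.** The SD of the between-arm difference in prior-GDM share is √(p(1−p)·2/60). At p = 0.40 this is √(0.24·2/60) = 0.089, or 9 points. For the chance of a gap of 10 points or more, take 48 of 120 women with prior GDM and let x of them fall in one arm. The gap is (2x−48)/60, so the event is |2x−48| ≥ 6 with x hypergeometric. The exact probability is 35%. It is 25% at a share of 20%, 34% at 35% and 36% at 50%.

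**Step 2: effect on the crude risk difference.** Shift = gap × (risk with prior GDM − risk without). For a 10-point gap and 16% risk without:
- 35% recurrence: 0.10 × 0.19 = 1.9 points
- 50%: 0.10 × 0.34 = 3.4 points
- 80%: 0.10 × 0.64 = 6.4 points

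With 30% risk without, the 50% case falls to 0.10 × 0.20 = 2.0 points.

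**Step 3: power.** Simulated trials with 60 per arm and a 40% share (100,000 per row) compared the chi-square with the Mantel-Haenszel test stratified by prior GDM, both without continuity correction. The stratified statistic is [Σ(aₖ − n₁ₖmₖ/Tₖ)]² / Σ[n₁ₖn₀ₖmₖ(Tₖ−mₖ)/(Tₖ²(Tₖ−1))]. In stratum k, aₖ is intervention-arm cases, n₁ₖ and n₀ₖ the arm sizes, mₖ all cases and Tₖ all women.

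| Recurrence | Risk without prior GDM | Chi-square | Stratified | Gain (points) |
|---|---|---|---|---|
| 35% | 16% | 53.6% | 55.5% | 1.9 |
| 35% | 25% | 64.6% | 64.3% | −0.3 |
| 50% | 16% | 58.0% | 61.8% | 3.8 |
| 50% | 25% | 68.4% | 69.5% | 1.1 |
| 50% | 30% | 72.7% | 72.8% | 0.1 |
| 70% | 16% | 52.2% | 63.2% | 11.0 |
| 70% | 25% | 63.0% | 70.7% | 7.6 |
| 70% | 30% | 67.7% | 73.9% | 6.3 |
| 80% | 16% | 42.2% | 59.3% | 17.1 |
| 80% | 25% | 54.1% | 67.6% | 13.5 |

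Gains are from unrounded values. With no treatment effect, rejection rates were 5.0 to 5.5% for the chi-square and 4.9 to 5.1% for the stratified test.

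**Cross-check.** A logistic simulation with and without prior GDM (3,000 runs, 50% recurrence, 16% risk without) gave 50 to 52%, 55 to 60% and 60 to 65% power at shares of 20%, 35% and 50%. Direction and size agree.

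**The case against.** The best defence is that this is a pilot sized on feasibility, and that randomisation already protects it. Chance imbalance is ordinary sampling variation, which the confidence interval covers. That stands. A reader might infer a biased comparison or an inflated false-positive rate, and Step 3 shows no such inflation.

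The gain also depends on unstated quantities. At the plan's own 50% recurrence it shrinks to nothing once women without prior GDM have a risk near 30%, and at 35% recurrence with 25% risk there is none. This stands too, and limits the claim.

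Other stronger readings are not supported:
- **That randomisation was unstratified.** Section 2.6 names no factor, and a single envelope sequence fits that reading, but a condensed article may leave strata to the full protocol.
- **That categorical BMI is a defect of similar weight.** No cut-points are given, the loss cannot be sized, and categories still correct part of any imbalance.
- **That the logistic model has too many terms for its events.** The number of BMI and parity categories is not stated, so the parameter count would be a guess, and the chi-square is unaffected.

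Finally, the wording of the list may not be exhaustive. But a list printed as decided a priori, with a main predictor absent, is a stated choice and not detail left to an unseen plan.

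**Conclusion.** The point holds as a modest, worthwhile correction. The adjusted analysis leaves out a predictor that the article itself ranks among the strongest, and that became variable only when eligibility was widened. The consequence is lost precision and chance imbalance that is not accounted for.

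The omission is clear from the text; the size of its cost is uncertain. Under the assumptions above (60 per arm, 40% with prior GDM, odds ratio 1/3), the power gain from stratifying is negligible to about 4 points at 35 to 50% recurrence, 6 to 11 at 70%, and about 14 to 17 at 80% with 16 to 25% risk in other women. The larger values need recurrence well above the 50% the plan assumed, so a reader should not take a double-figure gain as the expected case.

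**What to change.** Before unblinding, add prior GDM (yes/no) to the pre-specified logistic model, or specify a Mantel-Haenszel analysis stratified by it. Report that adjusted effect with a 95% CI, preferably as the main estimate, and keep the chi-square as the unadjusted result. If the full protocol does stratify allocation, say so in the analysis text. Entering BMI as a continuous variable is an optional refinement.

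The cost is analysis-plan wording only. The variable is already collected and describes earlier pregnancies, so it is a legitimate baseline covariate even though the questionnaire follows randomisation. One small downside is that nulliparous women and parous women without GDM share the same level (no prior GDM). A sensitivity model that includes parity can check whether this matters.
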